### Safety assessment

Participants will be asked to report any AEs, which are defined as any undesirable experiences [36]. They will have access to the research team members at any time. The occurrence time, severity, management, and causality of AEs will be recorded on CRFs. All AEs will be followed up until resolved, and severe AEs will be reported to the Ethics Committee of SCCGZUCM within 24 hours. Monitoring AEs in this trial serves the purpose of ensuring participant safety and dealing with adverse events in a timely manner, in addition to being a secondary outcome measure.

### Quality control and data management

To ensure adherence to the study protocol and familiarity with the administration process, all members involved in this program, including therapists, operational assistants, nurses, and statisticians, underwent systematic training before the trial commenced. The therapists responsible for applying the treatment possess Chinese medicine licenses, and both the therapists and nurses are familiar with the location of acupoints. All relevant information is recorded in CRFs, and the TNSS and RQLQs scales are carefully collected. Data entry follows the double-entry method using EpiData 3.1 software, and regular checks are performed to maintain data quality, with modifications recorded by a research assistant. Another research assistant conducts a double check of the data for any discrepancies and promptly notifies the manager if any are found. These two assistants are independent from the sponsor and have no competing interests with the authors. After repeated audits and logical checks to ensure the accuracy of the database, two sets of data will be locked and backed up for analysis. If participants withdraw from the trial at any stage, their reasons will be recorded, and the dropout rate will be analyzed statistically.

### Statistical analysis

Qualified statisticians who are blinded to the treatment group data will perform all efficacy and safety analyses following the intention-to-treat (ITT) principle using SPSS 20.0 (IBM SPSS Inc., Armonk, New York, USA). Missing values will be estimated using the last recorded data. A significance level of α= 0.05 will be considered statistically significant. The median, minimum, and maximum values will be used to express measured data. Group comparisons will be analyzed using Analysis of Variance (ANOVA) and pairwise comparisons (rank-sum test for univariate variance). Count data will be expressed as composition ratios or rates, and comparisons between groups will use the χ2 test for efficiency and rank-sum test for efficiency and rank-sum test for ranked data.

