### Sample size

The primary outcome measure is Total Nasal Symptom Score (TNSS). As there are no existing studies on ARAT, a new type of acupressure, the sample size calculation was based on a pilot study of ARAT for PAR that utilized the same outcome measure (Table 2). Using these results and considering the study's objectives, the sample sizes for the ARAT group and the non-specific acupoints group were separately calculated for comparison with the blank control group. The calculations were performed with α=0.05 and β=0.1, and the maximum sample size for each group was determined to be 33 cases using PASS11.0 (NCSS, LLC. Kaysville, UT, USA) software. Accounting for a potential 10% dropout rate, a total sample size of 111 participants will be recruited for this trial, with 37 participants allocated to each group.

**Table 2 Tab2:** Pilot study of ARAT for perennial allergic rhinitis

	**the ARAT group**	**the non-specific acupoints group**	**the blank control group**

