### Randomization and blinding

#### Randomization

The randomization sequence will be generated by the Key Unit of Methodology in Clinical Research at SCCGZUCM. The random numbers will be generated using the SAS statistical analysis system PROCPLAN process statement, with the numbers generated based on given seeds. The randomization process will be managed through computer network management, and a dedicated manager who is not involved in the study will control the distribution scheme. The eligible participants will be assigned random numbers in the order of their entry into the study, and the researchers will allocate them to the treatment group or control groups accordingly.

After collecting written informed consent, the 111 participants will be randomly divided into three groups, with 37 participants in each group.

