#### Drugs

Participants in all three groups will be administered the same medication, which is mometasone furoate nasal spray (50μg once daily, Zhejiang Xianju Pharmaceutical Co., Ltd., Batch number: H20113481), as the routine treatment during the intervention period. Additionally, for symptom control throughout the study, participants will use cetirizine hydrochloride tablets (10mg, Chengdu LEER Pharmaceutical Co., Ltd., Batch number: H20020250).

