Additionally, the treatment mechanism of ARAT will be explored in this trial. Nasal secretions from eligible participants will be collected by research nurses at the beginning and end of the treatment. These biological specimens will be centrifuged and stored in the Biological Resource Center of SCCGZUCM for molecular analysis. Cytokines such as interleukin-5 (IL5), IL13, thymic stromal lymphopoietin (TSLP), and interferon-gamma (IFN-γ) will be detected using the enzyme-linked immunosorbent assay (ELISA) method.

Among these outcome measures, TNSS and RQLQs will be assessed at the beginning, middle, and end of treatment period, as well as during the follow-up period at weeks 4, 8, and 12. The other measures will be assessed at the beginning and end of the treatment period.

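### Carrying the last score forward treats TNSS as static while it is falling, so the group difference depends on who drops out, when and in which arm

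*Protocol article*

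**What the plan says.** The Statistical analysis section says that analyses will be done "following the intention-to-treat (ITT) principle" and then gives its only missing-data rule: "Missing values will be estimated using the last recorded data". The rule is not limited to particular outcomes or visits.

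Under Secondary outcome measures, TNSS and RQLQs are scheduled at the start, middle and end of treatment, "as well as during the follow-up period at weeks 4, 8, and 12". That makes six assessments. The remaining measures, which include acoustic rhinometry, anterior rhinomanometry and the nasal cytokines, are taken only at the start and end of treatment.

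The Drugs section gives the nasal spray to all arms "as the routine treatment during the intervention period", and the acupressure course lasts 4 weeks. The Sample size section plans for dropout: "Accounting for a potential 10% dropout rate, a total sample size of 111 participants will be recruited for this trial". The Elimination criteria list, among others, participants who do not take full part in treatment or follow-up.

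**The concern.** LOCF gives the right mean only if scores would have stayed where they were last seen. The pilot in Table 2 shows otherwise: every arm improved during treatment, and ARAT improved most. An early score standing in for the end-of-treatment score removes part of the change from that arm's mean, in proportion to its dropout and to the change missed. The arms change by different amounts, and in an open-label trial with one arm receiving no acupressure they may also lose different numbers. The estimated difference then mixes treatment effect with dropout pattern.

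After week 4 the issue is different. A participant lost in follow-up keeps a score taken at the end of the treatment period for up to 12 further weeks.

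The article fixes this method rather than leaving it to an analysis plan, and it applies to the primary outcome.

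**Working it through.** **Plan's own figure.** 33 per group with 10% dropout: 33 / 0.9 = 36.7, rounded up to 37; 3 × 37 = 111. This agrees with the article. Ten per cent of 37 is 3.7 participants per arm.

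**Inputs from Table 2 (TNSS).**
- ARAT: 9.7 to 5.1, change −4.6
- Non-specific acupoints: 9.5 to 7.1, change −2.4
- Blank control: 10.1 to 7.3, change −2.8
- ARAT minus blank, difference in change: −4.6 − (−2.8) = −1.8

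**Assumptions (not in the documents).** Dropout is unrelated to outcome. The last score before loss is either baseline (share of the change already seen, f = 0) or week 2 (f = 0.5, taking half the change as reached by then). Unequal dropout splits are illustrative.

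**Formula.** Expected LOCF change in an arm with dropout d = change × [1 − d(1 − f)].

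| Dropout ARAT / blank | Baseline carried (f = 0) | Week 2 carried (f = 0.5) |
|---|---|---|
| 10% / 10% | −4.14 − (−2.52) = −1.62 | −4.37 − (−2.66) = −1.71 |
| 15% / 5% | −3.91 − (−2.66) = −1.25 | −4.255 − (−2.73) = −1.525 |
| 5% / 15% | −4.37 − (−2.38) = −1.99 | −4.485 − (−2.59) = −1.895 |

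The target in every cell is −1.8. Equal 10% dropout costs 0.09 to 0.18 points. The 15% / 5% split costs about 0.28 to 0.55 points, and 5% / 15% exaggerates the difference by about 0.1 to 0.2 points.

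**Two-visit outcomes.** With only a start and an end value, the last recorded value of anyone lost is baseline, so f = 0 and the imputed change is exactly zero.

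**False-positive rate.** Suppose both arms truly change by −2.8 and baseline is carried. With 5% against 15% dropout the spurious difference is 2.8 × (0.15 − 0.05) = 0.28 points in size. Simulating two-group comparisons (37 per arm, assumed SD 1.8, assumed between-visit correlation 0.5), the nominal two-sided 5% test rejects in about 9–10% of trials. With 10% in both arms it stays near 5%. With a true difference of −1.8 and a 15% / 5% split, the nominal 95% interval covers the truth in about 81% of trials.

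**Standard error.** With 37 complete participants per arm it is 1.8 × √(2/37) = 0.4185.
- If means are flat, LOCF reports about 0.417 at 10% or 20% dropout, against 0.440 and 0.467 for complete cases. Imputed values are being counted as observed.
- If baseline is carried and the changes are as large as in the pilot, the LOCF standard error at 10% dropout is about 0.48, above the complete-data value.

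**Follow-up (conditional).** Suppose the −1.8 advantage has vanished by week 12 and equal proportions are lost straight after treatment. LOCF then still shows 0.10 × −1.8 = −0.18 at 10% loss and 0.20 × −1.8 = −0.36 at 20%. If half the advantage remains (−0.90), LOCF shows 0.9 × −0.90 + 0.1 × −1.8 = −0.99 at 10%.

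**The case against.** The best defence is that at the planned dropout, equal in the arms, the harm is small: 0.1 to 0.2 points toward no difference, with the type I error kept. The documents give no sign of a split between arms. The lack of blinding makes one plausible but sets neither its size nor its direction. Reasons for withdrawal will be recorded and dropout analysed. All of this stands, and it limits the stated size. It does not rescue the rule, whose validity depends on a dropout pattern that nobody knows in advance.

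A second defence is that the elimination criteria could remove incomplete participants and leave LOCF little to fill. That would contradict the intention-to-treat statement, so it shows a further conflict and is no remedy.

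Three stronger readings are tempting, and the documents do not support them:
- A reader might infer that LOCF always makes standard errors too small. It does not: with baseline carried and large changes, the standard error exceeds the complete-data value.
- A reader might infer that LOCF will make the benefit look durable in follow-up. That holds only if the benefit wanes, and the article gives no scores after the end of treatment.
- A reader might infer a bias that always favours ARAT, or one that is always conservative. The sign changes with the dropout split.

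**Conclusion.** The concern holds in this limited form. LOCF is the article's only missing-data rule, and its assumption of static scores is contradicted by the pilot. At end of treatment the pilot difference of −1.8 becomes about −1.6 to −1.7 with equal 10% dropout. It becomes about −1.25 to −1.53 or −1.9 to −2.0 if dropout is 15% / 5% in one direction or the other. The type I error can roughly double under the 5% against 15% split. Intervals can misstate uncertainty about the true effect because imputed scores count as data.

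These sizes rest on the pilot means, dropout unrelated to outcome, half the change reached by week 2 and illustrative splits. The error rates also rest on SD 1.8 and correlation 0.5. That LOCF is fixed in the plan is certain; the size of the harm is not. The plan should be changed, but the trial's design and sample size do not depend on it.

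**What to change.** 1. Delete the last-recorded-value sentence from the Statistical analysis section.
2. Analyse TNSS and RQLQs with a likelihood-based mixed model for repeated measures over all scheduled post-baseline visits: arm, visit, arm-by-visit, baseline score, unstructured covariance. Take the end-of-treatment contrast for TNSS as primary.
3. For outcomes measured only at the start and end of treatment, use a baseline-adjusted analysis with multiple imputation, so that removing LOCF does not leave them without a rule.
4. Add one delta-adjusted multiple-imputation sensitivity analysis of the primary outcome. It should include participants with no post-baseline score, who contribute nothing to the model in item 2.
5. Reconcile the Elimination criteria with the intention-to-treat statement, so that participants who do not complete treatment or follow-up stay in the analysis.

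The cost is a little more analysis work on data already scheduled for collection, with no change to sample size or significance level. The drawback is reliance on data being missing at random, which the sensitivity analysis in item 4 is there to test.

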**Methods/design:**

In this trial, eligible 111 participants diagnosed with PAR will be randomly assigned to one of three groups: the ARAT group, the non-specific acupoints group, or the blank control group. The primary outcome will be the change in the total nasal symptom score, and the secondary outcomes will include: 1) changes in the scores of the standard version of Rhinoconjunctivitis Quality of Life Questionnaire (RQLQs); 2) acoustic rhinometry and anterior rhinomanometry; 3) changes in the scores of relief medication usage; 4) incidence of adverse events. Additionally, we will measure and compare the changes in cytokine levels (IL-5, IL-13, IFN-γ, and TSLP) in nasal secretions.

The RQLQs and primary outcomes will be assessed at the beginning, middle, and end stages of the treatment period, with monthly follow-ups conducted over a total of three months. The secondary outcomes and biomarkers in nasal secretions will be measured at the beginning and end of the treatment period. Any adverse events or need for rescue medication will be carefully noted and recorded.

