### Outcomes

This clinical trial will assess primary and secondary outcome measures. The outcomes will be compared between the groups at baseline, at the end of the treatment period, and at the end of the follow-up period. The recruitment, intervention, and assessment schedule for the randomized controlled trial is presented in Table 1.

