#### Primary outcome measures

The primary outcome measure for this clinical trial will be TNSS. TNSS evaluates four nasal symptoms: nasal obstruction, running nose, sneezing, and nasal itch. Participants will self-assess and record the severity of their symptoms using a four-point scale (0 = no symptoms; 1 = mild symptoms; 2 = moderate symptoms; 3 = severe symptoms) [3, 28]. TNSS scores range from 0 to 12, , with lower scores indicating milder nasal symptoms. Previous studies [29, 30] have utilized the TNSS as an assessment tool.

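### Groups are compared without adjustment for baseline TNSS, and the response (change or score) is not settled: a valid plan, but less precise than a baseline-adjusted model

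*Protocol article*

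**What the plan says.** The Statistical analysis section fixes the method: "Group comparisons will be analyzed using Analysis of Variance (ANOVA) and pairwise comparisons (rank-sum test for univariate variance". It also fixes the summaries: "The median, minimum, and maximum values will be used to express measured data". No covariate is named for any outcome.

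Baseline TNSS will be available. The Secondary outcome measures section states: "Among these outcome measures, TNSS and RQLQs will be assessed at the beginning, middle, and end of treatment period".

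The response is described in three ways:

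- Abstract, Methods/design: "The primary outcome will be the change in the total nasal symptom score".
- Primary outcome measures: "The primary outcome measure for this clinical trial will be TNSS", with no mention of change.
- Outcomes: "The outcomes will be compared between the groups at baseline, at the end of the treatment period, and at the end of the follow-up period". This reads as raw scores compared visit by visit, baseline included.

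The Sample size section says "the sample sizes for the ARAT group and the non-specific acupoints group were separately calculated for comparison with the blank control group" and "The calculations were performed with α=0.05 and β=0.1". It does not say whether post scores or changes from the pilot were used.

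**The concern.** Two things are at stake.

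The first is precision. A baseline measure of the primary outcome is usually its strongest predictor. ANOVA on post scores does not use it. ANOVA on change uses it with a fixed coefficient of 1, which is generally not the best weight. Letting the model estimate the coefficient gives a smaller variance in large samples, or at worst the same variance less one degree of freedom.

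The second is clarity. When arms differ by chance at baseline, post scores and change scores give different estimates. The article leaves both open in a trial where participants score their own symptoms without blinding, so the choice should be fixed in advance.

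The summaries add to this. A median with minimum and maximum does not describe the means that ANOVA compares, and gives no SD or confidence interval. The pilot table itself uses a mean ± format.

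**Working it through.** **Inputs.** From Table 2, TNSS pre and post: ARAT 9.7±2.2 and 5.1±1.7; non-specific 9.5±2.0 and 7.1±1.9; blank 10.1±1.7 and 7.3±1.6. The table does not label the ± figure; it is taken as an SD. From Sample size: α 0.05 (two-sided assumed), power 0.90, 33 evaluable and 37 randomised per group. The pre-post correlation r is not given; 0.3, 0.5 and 0.7 are assumed.

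**The plan's own figure.** 33/0.9 = 36.7, so 37 per group and 3 × 37 = 111. That reproduces. The 33 does not reveal the intended response. ARAT versus blank needs 12 per group on post scores, and reaches 33 on change scores only if r is about 0.25. Non-specific versus blank needs 1,621 on post scores. That mismatch is a separate matter, and nothing below depends on it.

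**Dependence on the scale.** Mean falls are 9.7-5.1 = 4.6 (ARAT), 9.5-7.1 = 2.4 (non-specific) and 10.1-7.3 = 2.8 (blank).

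| Comparison | Post scores | Change |
|---|---|---|
| ARAT vs blank | 7.3-5.1 = 2.2 better | 4.6-2.8 = 1.8 better |
| ARAT vs non-specific | 7.1-5.1 = 2.0 better | 4.6-2.4 = 2.2 better |
| Non-specific vs blank | 7.3-7.1 = 0.2 better | 2.4-2.8 = 0.4 worse |

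ANCOVA does not depend on this choice. Subtracting baseline from the response only lowers the baseline coefficient by 1; the treatment estimate is unchanged.

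**Precision against post scores.** The variance ratio is 1-r²: 0.91, 0.75 and 0.51. At r = 0.5, 33 evaluable per arm carry the information of 33/0.75 = 44.

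**Precision against change scores.** With equal pre and post SDs the ratio is (1-r²)/[2(1-r)] = (1+r)/2: 0.65, 0.75 and 0.85. The pilot SDs are not equal. In the ARAT arm at r = 0.5:

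- ANCOVA residual variance: 1.7² × 0.75 = 2.17.
- Change variance: 2.2² + 1.7² - 2 × 0.5 × 2.2 × 1.7 = 3.99.
- Ratio: 2.17/3.99 = 0.54, not 0.75.

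Where the baseline SD is the larger, the equal-SD formula therefore understates the gain over change scores.

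**What it means for ARAT versus blank** (pilot values, two-sided 0.05). The formula is n per group = 2 × (1.960+1.282)² × SD²/difference². For post scores, SD² = (1.7²+1.6²)/2 = 2.725, so n = 2 × 10.51 × 2.725/2.2² = 11.8, rounded up to 12. For ANCOVA, SD² is multiplied by 1-r², and the difference is the post difference less r × (post SD/pre SD) × the baseline difference. At r = 0.5 that is 2.2 - 0.42 × 0.4 = 2.03.

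| Assumed r | n, post | n, change | n, ANCOVA | Power at 33, change |
|---|---|---|---|---|
| 0.3 | 12 | 31 | 12 | 0.92 |
| 0.5 | 12 | 22 | 11 | 0.98 |
| 0.7 | 12 | 14 | 8 | >0.99 |

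Power at 33 per group on post scores and by ANCOVA exceeds 0.99 throughout.

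**Noise in the third comparison.** At 37 per arm the standard error for non-specific versus blank is 1.756 × √(2/37) = 0.41 on post scores, and 1.808 × √(2/37) = 0.42 on change at r = 0.5. Both estimates, 0.2 and 0.4, lie within about one standard error of zero.

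**The case against.** The strongest reply is that nothing here is wrong in the sense of invalid. Randomisation makes unadjusted ANOVA unbiased, the trial calls itself exploratory, and on the pilot effect ARAT versus blank has ample power. A condensed article may also leave model details to an analysis plan that is not shown. The first part stands and limits the size of the point. The second stands only for details such as robust standard errors or transformation of cytokines, which are not raised here. The article does state its method and summaries, and a later plan would have to follow that text or depart from it.

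A reader might infer more than the document supports:

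- That baseline is ignored. On the abstract's definition it enters by subtraction. It is then used, though not adjusted for. The outcome section may also be naming the instrument and the abstract the metric, so this is a response left unsettled rather than a flat contradiction.
- That the reversal for non-specific versus blank shows the choice of scale would change the trial's conclusion. Both values are within noise, and Table 2 flags differences from the ARAT arm only. The reversal is an illustration. Both ARAT comparisons keep their direction.
- That the rank-sum test is offered as a cure for unequal variances. The parenthesis is too garbled to say what it means. What can be said is that the rule for choosing between ANOVA and rank-sum cannot be read from the text.

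**Conclusion.** The point holds as a recommendation on efficiency and clarity. The stated analysis has no baseline adjustment, and the article does not settle whether change or score is analysed. In the pilot that choice moves the ARAT versus blank estimate between 2.2 and 1.8 points.

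Adjustment would cut the variance to between 91% and 51% of the post-score value for r between 0.3 and 0.7. Against change scores it would cut it to between 65% and 85% under equal SDs, and further where the baseline SD is larger (about 54% in the ARAT arm at r = 0.5). These sizes rest on an assumed r. Against post scores the gain is small if r is low.

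It would be wrong to conclude that the primary comparison is biased or that the missing covariate leaves it underpowered: at the full pilot effect, post-score power at 33 per group exceeds 0.99. The gain counts mainly if the true effect is smaller than in the pilot, or if change scores are analysed.

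**What to change.** State one primary analysis: a linear model of end-of-treatment TNSS with arm and baseline TNSS as terms. Use the same response wording in the abstract, the outcome sections and the analysis section. Report adjusted mean differences in TNSS points with 95% CIs, and mean (SD) by arm in place of median, minimum and maximum alone. Use the same approach for the other continuous outcomes that have a baseline value. Keep the rank-sum test as a sensitivity analysis, and rewrite the parenthesis that introduces it.

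The cost is one degree of freedom and a change of wording. TNSS is already measured at the start of treatment, and the named software can fit the model. Because the article is published, the change should be dated and made before the data are analysed.
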